In **Phase III**, the final model shall be implemented across the district at each of the sites. The primary evaluation outcome is facility-level coverage of the mental health screening and management strategy. We require an estimate of coverage of 70% with an absolute precision of ±10% and 95% confidence. Using the single-proportion formula n = Z^2^ p (1 − p)/ d^2^, with Z = 1.96, p = 0.70, and d = 0.10, gives n = 80.7, rounded up to 81 health facilities per district. The implementation cascade was designed such that screening, referral, and management rates of ≈90% at each step yield an overall coverage of 0.9 × 0.9 × 0.9 = 0.729 (≈72.9%), which is slightly conservative with respect to the 70% target. Because the primary unit of analysis is the facility, this sample-size calculation does not require an intra-cluster correlation correction; however, if analyses are to be performed at the individual level or if clustering is a concern, the sample will be inflated by an appropriate design effect (DEFF = 1+ (m − 1) ρ), and allowance will be made for anticipated non-response. A sensitivity analysis using DEFF values between 1.2 and 1.5 and a 10% non-response adjustment is presented in Supporting Information S1 Table. (S1 Table – Sensitivity Table using Appropriate Design Effect)

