(1) Tools for integrated screening and assessment for mental health conditions shall be developed for all levels of healthcare personnel. These shall include the screening tools to be used by Accredited Social Health Activists (ASHA) and Community Health Officers (CHOs) and assessment tools to be used by the Medical Officers (MO). The screening tools shall be developed by the ICMR HQ in consultation with mental health experts. The assessment tools for the MOs shall be developed by the participating sites. These screening and assessment tools shall be developed for emergency mental health conditions, common mental disorders (depressive disorder and anxiety disorder), substance use disorder (tobacco and alcohol use disorder), and self-harm. The proposed screening tool shall be based on the mhGAP intervention guide (by the World Health Organization), Patient Health Questionnaire-9 (PHQ-9) [22], and the Generalized Anxiety Disorder-7 (GAD-7) [23] and shall include a screener for tobacco, alcohol, and other psychoactive substances [24], which will be translated to local languages in each state and validated before using it. The PHQ-9 and GAD-7 are validated scales and available in local languages. The assessment tools shall be based on the recent version of the diagnostic system, viz., International Classification of Diseases (ICD)-11. All the tools will be administered in an interview format.(2) The workflows and pathways that integrate mental health interventions within NCD care shall be developed. These shall be developed by the ICMR HQ and the study sites. These shall be based on the WHO mhGAP intervention guide [25] and other guidelines on the management of MSUDs. In order to ensure the applicability to the local context, the recommendations made by various organizations, associations, and departments in the county shall be taken into consideration. The ICMR Standard Treatment Workflow of India for Psychiatry [26] and the ICMR Community Health Officers’ Mental Health Workflow shall be some of the resources (S1 Fig). Drug interactions shall be considered while drawing up a management plan. Screening, assessment (diagnosis and severity of the disorder), and management (treatment and referral) shall constitute the intervention package. All aspects of the intervention package shall be translated into the local languages.(3) A digital platform and smartphone app shall be developed. These shall be developed for various purposes, including the digitization of the screening tools, referral and management protocols using an electronic decision support system; tracking of the number of participants screened, treatment initiated in screen positives, number of follow-ups by the participants, number of participants linked to CHC, District, and Hospitals; care coordination mechanisms for effective communication and referral systems using recall and reminder systems; and monitoring and evaluation of the project.

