**b) Mixed Methods Evaluation Using CFIR and IRLM:**

The implementation model (M0) will be evaluated using a combination of qualitative and quantitative methods, guided by the Consolidated Framework for Implementation Research (CFIR) [32] (Table 2) and the Implementation Research Logic Model (IRLM) (Table 3) [33]. These frameworks will help identify the constructs that contribute to or hinder the integration of MSUD services within NCD care across different settings. The IRLM will support mapping the inputs, activities, outputs, and outcomes, while the CFIR constructs will guide data collection on implementation processes and context.

**Table 3 pone.0332359.t003:** Pre-facility, facility, and post-facility components of the logic model and specific aspects of the logic model for the implementation framework.

	Pre-Facility	Facility		Post-facility	
Objectives	Identifying study sites Addressing stigma Human resources	Integrate screening, diagnosis, treatment, and linkage within the health system, monitoring of treatment adherence		Sustainability of screening and treatment for mental health conditions Integrated care being scaled up at the state level	
Activities	Stakeholder’s meetings Community engagement Capacity building workshops	Stakeholder’s meetings Involve policymakers Community engagement Capacity building of relevant HCWs, workshops Creating an online platform for seamless data collection and integration		Identify barriers of sustainability and scaling up Collaboration with policymakers and other stakeholders Budgetary allocation	
Personnel involved	Policymakers, health department, community leaders, HCW	ASHA workers, ANM, CHO, MO Private doctors		Policymakers Health department officials	
Outcomes	Increased public awareness and reduced stigma Availability of trained human resources	At least 70% screening for target mental health conditions among people seeking care for NCD At least 70% of those screened positive, get appropriate treatment and linkage to care. Screening and treatment are acceptable, feasible, adoptable, and affordable		Adoption and scaling up of the integrated care at the state level	

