### Study outcomes

#### Primary outcomes.

The primary outcomes of the study are

Proportion of individuals screened for CMD and SUD among those seeking care for NCDsProportion of those screened positive who are successfully referred and linked to appropriate mental health or substance use disorder services.Proportion of those linked to care who initiate evidence- based treatment and support.

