**Feasibility (Yes/No)** (compatible or actual fit) The extent to which an intervention can be carried out in a particular setting or organization	Facility and Individual providers Organization or setting	• Quantitative assessments from the Healthcare facility registers and government databases.	• Proportion of patients screened for MSUD among those screened/confirmed with NCD (N + M) • Proportion of screened positive/confirmed for MSUD managed, are under follow up, complied with referral
**Fidelity** The degree to which an intervention was implemented as it was designed in an original protocol, plan, or policy	Facility and Individual provider (adherence, quality of delivery, program component differentiation, exposure to the intervention, and participant responsiveness or involvement)	• Quantitative assessments from the Health care facility registers and government databases.	• Proportion of facilities who started integrating the model • The proportion of patients who initiated the treatment, following up with the health facility • The proportion of the patients in whom the continuum of care was ensured.
**Penetration** (integration of a practice within a service setting and its subsystems)	Organization or setting Facility level: The integration of MH screening in NCD within public health system; (the extent to which MH screening, linkages and treatment completed)	• Quantitative assessments from the Health care facility registers and government databases.	• Proportion of NCD patients screened for MSUD ◦ numerator assessed with patients registered in the digital App/ record review ◦ denominator assessed with HWC/PHC/CHC register (patients with NCD registered at the facility) • Among those with a positive MSUD screen ◦ proportion who are screened, managed and referred ◦ numerator assessed with patients registered in the digital App/ record review ◦ denominator assessed with HWC/PHC/CHC register (patients with NCD registered at the facility)

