### Statistical analysis

#### Quantitative analysis.

Data analysis would be done with IBM SPSS software (Version 25.0) and R software (Version 4.5.1). Nominal or categorical variables would be summarized as frequency and percentage. Continuous variables will be summarized as mean and standard deviation when normally distributed and as median and interquartile range (IQR) when non-normally distributed. We shall assess the percentage of the cases seeking NCD care who shall be offered screening, linkage to care, and management of common mental disorders and substance use disorders following the implementation model. Appropriate statistical analyses will be conducted based on the type of data and study design. Comparisons of mean scores between two independent groups will be performed using the independent samples t-test or the nonparametric equivalent if the assumption of normality is violated. For comparisons involving more than two independent groups, one-way ANOVA will be employed. To assess changes in outcome measures over time within subjects, one-way or two-way repeated measures ANOVA will be used, depending on the number of within- and between-subject factors. For categorical variables, associations between independent groups will be examined using the Chi-square test, while the McNemar test will be applied to assess changes in paired categorical data (e.g., pre- and post-intervention). Comparisons of paired quantitative data, such as baseline and post-intervention measurements within the same group, will be conducted using the paired t-test or its nonparametric alternative, such as the Wilcoxon signed-rank test, depending on data distribution. A two-tailed test will be employed. P < 0.05 will be taken to be the statistical significance level. If clustering of variables is detected during analysis, cluster analysis techniques will be employed to explore these patterns.

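### The analysis section assesses the percentage of NCD care seekers who are offered services, whereas the primary outcomes count people screened, linked and starting treatment, each with its own denominator

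*Protocol article*

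**What the plan says.** **Analysis.** In the protocol article, the Quantitative analysis section under Statistical analysis says: "We shall assess the percentage of the cases seeking NCD care who shall be offered screening, linkage to care, and management". The conditions concerned are common mental disorders and substance use disorders. The rest of the section gives general summaries and tests, and no other sentence there names a coverage quantity.

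**Primary outcomes.** The Primary outcomes section lists three proportions. The first is people screened out of those seeking NCD care. The second is people who were referred and actually reached services, out of those screening positive. The third is "Proportion of those linked to care who initiate evidence- based treatment and support".

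**Targets.** Table 3 sets the 70% targets in the same terms: "At least 70% screening for target mental health conditions among people seeking care for NCD" and "At least 70% of those screened positive, get appropriate treatment and linkage to care". Its second part repeats a 70% target at every level of the care cascade.

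**Data.** Under Intervention components, the app's functions include "tracking of the number of participants screened, treatment initiated in screen positives", together with follow-ups and numbers linked to higher facilities. For Penetration, Table 7 specifies "numerator assessed with patients registered in the digital App/ record review".

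**The concern.** An offer is something the provider does. Being screened, reaching a service and starting treatment are things that happen to the patient. Someone who is offered a service and declines, or does not attend, is a success in the analysis sentence and a failure under the primary outcomes. The protocol does not treat the two as the same elsewhere. In Table 8, one item concerns screen positives who are offered an intervention or referred by the CHO, another counts those started on treatment, and another counts patients who do not reach the next referral point. Table 7 looks at compliance with referral.

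The denominators differ as well. The analysis sentence applies one denominator to all three services, while the primary outcomes narrow it at each step.

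The design is single-arm with no control group, and the primary objective is coverage of at least 70%. What enters the numerator and denominator can therefore decide whether the objective is met. As the text stands, an analyst could follow either section and claim to have followed the protocol.

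**Working it through.** **1. The plan's own figures.** The Sample size section gives p = 0.70, d = 0.10 and Z = 1.96: n = 1.96² × 0.70 × 0.30 / 0.10² = 80.67, rounded up to 81 facilities per district. The cascade is 0.9 × 0.9 × 0.9 = 0.729. Both reproduce. Neither supplies an offer rate or an acceptance rate: the cascade is described as "screening, referral, and management rates of ≈90% at each step yield an overall coverage of 0.9 × 0.9 × 0.9 = 0.729".

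**2. The two definitions side by side.**

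| Step | Analysis sentence | Primary outcome |
|---|---|---|
| Screening | offered / NCD care seekers | screened / NCD care seekers |
| Linkage | offered / NCD care seekers | linked / screen positives |
| Treatment | offered management / NCD care seekers | treatment started / those linked |

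The numerator differs in all three rows. The denominator differs in the second and third.

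**3. Direction on a common denominator.** Let N be the denominator, O the number offered and a the share of those offered who accept and attend. The number receiving is R = O × a. Because a ≤ 1, R/N ≤ O/N. The offer-based percentage equals the receipt-based one only if nobody declines or fails to attend.

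**4. Illustration for screening, where the denominators agree.** The documents give no value for a, and both offer levels below are also assumptions. Percentage screened = percentage offered × a.

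| Acceptance a | 75% offered | 90% offered |
|---|---|---|
| 100% | 75.0% | 90.0% |
| 95% | 71.25% | 85.5% |
| 90% | 67.5% | 81.0% |
| 80% | 60.0% | 72.0% |
| 70% | 52.5% | 63.0% |

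Screening falls below 70% once acceptance is under 0.70/0.75 = 93.3% in the first column, or under 0.70/0.90 = 77.8% in the second. In both columns the offer-based figure stays above 70% throughout.

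**5. The denominator for linkage and treatment.** Linked / all care seekers = (screened / all) × (positive / screened) × (linked / positive). If linkage concerns screen positives only, this product cannot exceed the share of care seekers who screen positive, however good linkage is. The single denominator thus gives a different quantity from the second and third primary outcomes, and it pulls the percentage down while counting offers pushes it up. The net direction for those two outcomes is not determined. The statement that offers can only overstate holds on a common denominator, as in screening.

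**The case against.** The strongest reply is that *offered* is loose drafting. The analysis sentence mentions neither the 70% target nor the primary outcomes. Those outcomes and the targets are fixed by receipt elsewhere. The same section says categorical variables will be summarised as frequencies and percentages, which would cover the primary proportions. The app's listed functions cover people screened, linked and treated, not offers, and Table 8 reports drop-outs separately. This makes a receipt-based analysis the likelier intention, and that part stands. It does not remove the conflict: the one sentence that says what will be assessed names a different quantity, and no section says which prevails.

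Some stronger readings are tempting but not supported:

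- A reader might infer that the trial will judge its 70% target on offers. Nothing states this.
- A reader might treat the 90% step rates in the Sample size section as offer rates and deduct refusals at each step. They are described as rates of screening, referral and management, so the deduction has no basis there.
- A reader might take the 10% non-response in that section as a refusal rate. It is an allowance for inflating the sample. The 10% in the illustration above is a free assumption.
- A reader might set the gap against the stated precision, "We require an estimate of coverage of 70% with an absolute precision of ±10% and 95% confidence". That figure concerns sampling of facilities in a district and is no yardstick for a difference in how patients are counted.

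**Conclusion.** The point holds as a contradiction between the analysis sentence and the primary outcomes, in both numerator and denominator. Followed literally, the sentence would not estimate any of the three primary outcomes. For screening, where the denominators match, the error can only be upward, and the reported figure could pass 70% when the proportion screened does not. The illustration of 75% offered against 67.5% screened rests on an assumed offer level and an assumed 10% declining; with full acceptance there is no gap. The true size cannot be derived from the documents. Severity is moderate: the wording bears on the primary objective of an uncontrolled study, but the outcome definitions are sound and the planned data point to receipt.

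**What to change.** Replace the whole analysis sentence, not only the word *offered*. Changing that word alone would leave NCD care seekers as the denominator for linkage and treatment. The new text should say that the analysis estimates the three primary-outcome proportions:

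- people screened, out of those seeking NCD care;
- people referred and linked, out of those screening positive;
- people starting treatment, out of those linked.

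It should add that refusal and non-attendance count as not covered, and that any percentage offered is reported separately as a process indicator.

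The cost is one sentence. The app is already planned to track the receipt counts, so no new data are needed, and the 81 facilities per district are unaffected. Reported coverage may be less favourable than an offer-based figure would have been. The change should be made before the final analysis, since recruitment began in May 2025.

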## Materials and methods

### Study design

It is a multi-site implementation research study employing a mixed-methods, single-arm, quasi-experimental interrupted time series design with a pre-post approach conducted within-site over three phases and without a control group. The study would incorporate formative and evaluative components into iterative improvement cycles.

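### The design is declared an uncontrolled interrupted time series, but every test named is a before-after or group comparison that does not model the pre-implementation trend

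*Protocol article*

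**What the plan says.** The Study design section fixes a "single-arm, quasi-experimental interrupted time series design with a pre-post approach conducted within-site over three phases and without a control group".

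The Quantitative analysis section opens with a general clause: "Appropriate statistical analyses will be conducted based on the type of data and study design". It then lists the tests:

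- Independent-samples t-test and one-way ANOVA for independent groups.
- For change over time: "To assess changes in outcome measures over time within subjects, one-way or two-way repeated measures ANOVA will be used".
- Chi-square where the categories being compared come from separate groups.
- Where categorical observations are paired, the rule reads: "the McNemar test will be applied to assess changes in paired categorical data (e.g., pre- and post-intervention").
- A paired t-test, or Wilcoxon if normality fails, for continuous measurements taken twice on the same units.
- The decision rule: "A two-tailed test will be employed. P < 0.05 will be taken to be the statistical significance level".

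The one sentence in that section specific to coverage is descriptive: the percentage of NCD attendees offered screening, linkage and management once the model is in place.

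The three primary outcomes are proportions of individuals: screened among NCD attendees, linked among those who screen positive, and treated among those linked. The Sample size section, however, names the facility as the primary unit of analysis. In Table 7, the Penetration row gives the source of the screening count as "numerator assessed with patients registered in the digital App/ record review", over a register denominator.

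**The concern.** In a single-arm study, the series of observations before implementation is the main protection against secular change. An interrupted time series projects the pre-implementation trend forward and asks whether level or slope departs from it. None of the named tests does this. Paired t, Wilcoxon and McNemar compare two occasions. Repeated-measures ANOVA treats time as a set of occasions and tests whether their means differ, so a steady drift counts as change.

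The protocol itself gives reason to expect drift. The Introduction describes a national programme that is widening primary care to include mental health. The Context row of Table 6 plans to log MSUD trainings in the district run outside the project. Nothing in the analysis section uses that log.

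At stake is the causal part of the message. The primary objective is a model that brings about high coverage, and the Conclusion speaks of enhancing coverage. Whether the model did so cannot be answered by the listed tests.

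**Working it through.** **1. The plan's own figure.** The Sample size section uses Z = 1.96, p = 0.70 and d = 0.10:

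n = Z² p(1 − p)/d² = 3.8416 × 0.21 / 0.01 = 80.7, rounded up to 81 per district; 7 × 81 = 567.

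Both figures reproduce. They concern the precision of one post-implementation proportion and supply no input for a pre-post or time-series contrast.

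**2. Design against tests.**

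| Needed for an interrupted time series | Named in the article |
|---|---|
| Pre-implementation trend | No |
| Level change at start | No |
| Slope change after start | No |
| Number and spacing of time points | No |

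Number and spacing of points, and the handling of autocorrelation, may reasonably sit in an analysis plan that is not shown. The finding rests on the tests that are stated.

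**3. Bias of a before-after contrast under drift.** Take k months before, k months after, a linear trend of b points per month and no effect. For k = 12, with months numbered 0 to 23, the mean month is 5.5 before and 17.5 after. The apparent change is (17.5 − 5.5) × b = 12b; in general it is k × b. Both k and b are assumptions:

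| b (points/month) | k = 6 | k = 12 |
|---|---|---|
| 0.25 | 1.5 | 3 |
| 0.5 | 3 | 6 |
| 1.0 | 6 | 12 |

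**4. Simulation at facility level.** Every input except the 81 facilities (one district) is assumed: 12 + 12 months, coverage 20% at the first month, between-facility SD 8 points, independent monthly residuals with SD 8 points, linear trend, true effect zero, 2000 runs per trend. The facility is the unit in both analyses, so patients within a facility are not counted as independent.

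| Trend (points/month) | Mean paired pre-post change (points) | Paired t-test rejects | Segmented level change rejects |
|---|---|---|---|
| 0 | 0 | 5.7% | 4.8% |
| 0.25 | 3.0 | 100% | 4.8% |
| 0.5 | 6.0 | 100% | 5.6% |
| 1.0 | 12.0 | 100% | 4.3% |

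The mean segmented level change stayed within 0.02 points of zero. The simulated trend is linear and has no autocorrelation, so this shows the mechanism; it does not forecast the trial.

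**5. Where pairing exists.** At patient level, the people seeking NCD care before and after are not a matched cohort, and the screened-positive and linked denominators are different sets of people in each period. McNemar and within-subject ANOVA have no pairs there. At facility level, coverage in the same facility before and after is a genuine pair for a paired t or Wilcoxon test. Table 7 measures adoption before and after by facility and provider, and Table 6 lists pre- and post-training tests of health workers; these can be paired too. Step 4 shows that valid facility pairing does not remove the trend bias.

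**The case against.** The strongest reply has four parts.

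*The tests are conditional and the plan defers to the design.* McNemar and the paired tests are reserved for paired data, chi-square is there for independent groups, and no test is assigned to the primary outcomes. This stands against a stronger reading that a reader might infer, namely that the protocol applies paired tests to unpaired coverage data. It does not say so, and its stated unit and within-site approach make facility pairing legitimate. The clause about study design does not rescue the trend point, because no test listed after it suits a time series.

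*The headline target is not a before-after contrast.* This stands. Coverage of at least 70% is a post-implementation percentage, and among the Table 8 patient outcomes only item 8 states a comparison with baseline. A reader might infer that drift could produce the 70% result. On the assumed inputs it could not: at 1.0 point per month the post-period mean is 20 + 17.5 = 37.5%.

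*The numerator source is not said to change.* Correct. Table 7 allows app or record review, and records can serve both periods. But the app is a component of Model 0, so a recording change coinciding with implementation is a risk to close off. It is not a stated rule.

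*Outside training is monitored.* It is, through Table 6, and that helps interpretation. Logging it does not adjust the estimate.

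**Conclusion.** The point holds in this form: the article declares an uncontrolled interrupted time series and names no analysis that uses the series. Any secular rise in screening would pass into the estimated effect of the model at k × b points, which is 3 to 12 points for the assumed 12-month windows and 0.25 to 1.0 point per month. The documents give no baseline coverage, trend, window length or number of time points, so the true size is unknown.

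The paired tests are suitable for facility- or provider-level items and unsuitable for the patient-level primary proportions. The descriptive coverage estimate against 70% stands without a time series. What lacks support is a statement that coverage improved because of the model.

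**What to change.** For any pre-post claim about coverage, state a segmented regression of periodic facility counts (screened out of NCD attendees), for example

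g(p_it) = α_i + β₁t + β₂Post_it + β₃(t − S_i)Post_it + district,

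where S_i is the start date at facility i, α_i is a facility random effect (or GEE is used), β₂ is the level change and β₃ the slope change.

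- Take the numerator from one source, record review, before and after.
- Analyse the pilot blocks that receive M0 to Mx separately from the Phase III roll-out, because they receive different models.
- Use later-starting blocks as a concurrent comparison only where start dates actually differ. The Phase III section describes implementation across all facilities and does not promise a staggered start.
- Keep McNemar and the paired tests for facility- or provider-level pre/post items.
- If periodic pre-implementation counts cannot be obtained from registers, drop the interrupted-time-series label and report coverage descriptively, without attributing change to the model.

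The cost is protocol or analysis-plan wording, extra register extraction and more analysis work. Registers are already a data source and R is already named, but no section confirms that periodic pre-implementation screening counts exist. That should be checked first.

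### The analysis section's only answer to clustering is exploratory cluster analysis, which does not correct patient-level standard errors, and the unit of analysis is not settled

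*Protocol article*

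**What the plan says.** The Quantitative analysis section lists t-tests, ANOVA, repeated measures ANOVA, Wilcoxon, chi-square and McNemar. For categorical data, "associations between independent groups will be examined using the Chi-square test", and "the McNemar test will be applied to assess changes in paired categorical data (e.g., pre- and post-intervention"). It adds: "A two-tailed test will be employed" and "P < 0.05 will be taken to be the statistical significance level". On coverage it says: "We shall assess the percentage of the cases seeking NCD care who shall be offered screening". Its one sentence on clustering is: "If clustering of variables is detected during analysis, cluster analysis techniques will be employed to explore these patterns".

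The Primary outcomes section defines three proportions of individuals: those screened among people seeking NCD care, those linked among people who screen positive, and those starting treatment among people linked.

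The Sample size section takes a different unit: "Because the primary unit of analysis is the facility, this sample-size calculation does not require an intra-cluster correlation correction". It then adds a condition: "if analyses are to be performed at the individual level or if clustering is a concern, the sample will be inflated by an appropriate design" [...]. The inflation factor it means is DEFF = 1 + (m − 1)ρ. It refers to a supporting table that uses design effects of 1.2 to 1.5 and 10% non-response.

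**The concern.** Clustering here is part of the design and needs no detection step. Patients are seen in 81 evaluated facilities in each of seven districts. Whether a patient is screened depends largely on whether that facility's staff have taken up the model, so outcomes within a facility will tend to be alike.

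The stated response has three weaknesses. It applies only if clustering is found. It speaks of variables, not patients. Its method is descriptive grouping, which does not touch variances. The design-effect clause in the Sample size section does not fill the gap, because enlarging the sample does not correct a naive standard error calculated from it.

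The main result will be judged against the 70% coverage target. If the intervals around the primary proportions ignore facility clustering, they overstate how firmly a district has met or missed that target. Comparisons between groups of facilities or between districts would be declared significant too often.

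**Working it through.** **The plan's own figure.** n = Z²p(1 − p)/d² = 1.96² × 0.70 × 0.30 / 0.10² = 80.67, rounded up to 81 facilities per district; 81 × 7 = 567. Both figures reproduce. The calculation treats each facility as one observation.

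**The sections side by side.**
- Sample size: unit is the facility, so no correlation correction.
- Primary outcomes: unit is the individual.
- Quantitative analysis: percentage of cases, so again the individual; no facility-level summary is named.

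By the Sample size section's own condition, individual-level analysis calls for an allowance for clustering. The analysis section does not supply one.

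**Effect of ignoring clustering on a patient-level proportion, or on a test between different sets of facilities.**
- True SE / naive SE = √DEFF
- True coverage of a nominal 95% interval = 2Φ(1.96/√DEFF) − 1
- True type I error of a nominal 5% two-sided test = 2[1 − Φ(1.96/√DEFF)]

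With the article's design effects:
- DEFF 1.2: √1.2 = 1.095, so the naive SE is 8.7% too small. 1.96/1.095 = 1.789, giving coverage 92.6% and type I error 7.4%.
- DEFF 1.5: √1.5 = 1.225, so the naive SE is 18.4% too small. 1.96/1.225 = 1.600, giving coverage 89.0% and type I error 11.0%.

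With assumed patients per facility m and correlation ρ (neither is in the article):

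| m | ρ | DEFF | Coverage | Type I error |
|---|---|---|---|---|
| 10 | 0.01 | 1.09 | 94% | 6% |
| 20 | 0.05 | 1.95 | 84% | 16% |
| 50 | 0.05 | 3.45 | 71% | 29% |
| 100 | 0.05 | 5.95 | 58% | 42% |

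In reverse, ρ = (DEFF − 1)/(m − 1). A DEFF of 1.5 corresponds to ρ of about 0.026 at m = 20, 0.010 at m = 50 and 0.005 at m = 100. With many patients per facility, even a small correlation takes the design effect beyond the article's range.

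**Simulation check.** Beta-binomial data, 81 facilities, p = 0.70, 4,000 replicates. At m = 50, ρ = 0.05 the naive interval covered 70% and an interval from between-facility variance covered 95%. Over m = 20 or 50 and ρ = 0.01 to 0.10, the between-facility interval covered 94% to 95% throughout.

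**Within-facility pre-post contrast.** Assume different patients in each period, the same facilities, and correlation r between a facility's effects in the two periods. The variance of the change relative to the naive variance is then 1 + (m − 1)ρ − mrρ. For m = 50, ρ = 0.05:
- r = 1: 3.45 − 2.50 = 0.95, type I error about 4%
- r = 0.8: 3.45 − 2.00 = 1.45, about 10%
- r = 0.5: 3.45 − 1.25 = 2.20, about 19%
- r = 0: 3.45, about 29%

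The single-proportion figures are therefore an upper limit for pre-post tests when r lies between 0 and 1. The values of r are assumptions.

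**The case against.** The strongest reply is that the Sample size section names the facility as the primary unit. If each facility contributes one coverage value, within-facility correlation does no harm, and paired t-tests or Wilcoxon tests across facilities are sound cluster-summary analyses. That is correct as statistics. It does not describe the plan as written, because the outcomes and the analysis section work with individuals and no facility summary is named.

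A second reply is that the sentence about variables may describe only an exploratory exercise, with handling of clustering left to a fuller document. Detail may indeed be left there. But on that reading the sentence is no provision for clustered patients at all. On the other reading it prescribes a method that cannot do the job. The conflict over the unit remains either way.

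A reader might go further and infer that patient-level results will be far too optimistic, that every patient-level P value below 0.05 is invalid, or that all the named tests assume full independence. The article does not support these:
- It gives neither m nor ρ, and at its only stated design effects the error is moderate.
- The study is a within-site pre-post design, and stable facility effects partly or wholly cancel in such contrasts.
- McNemar, the paired tests and repeated measures ANOVA do handle dependence within a unit; what they assume is independence between units.
- No interval method is specified, so the concern is with intervals calculated in the usual binomial way.

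**Conclusion.** The point stands in a limited form. The only clustering provision in the analysis section cannot correct standard errors for patients sharing a facility, and the article gives two different units of analysis. Patient-level coverage intervals, and tests between facilities or districts, would be too optimistic. At the article's design effects the naive standard error is 9% to 18% too small, and a 5% test errs at up to roughly twice its nominal level. That result assumes that the 1.2 to 1.5 range applies to the patient-level analysis and that no adjustment is made.

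Severe undercoverage, such as 71% at m = 50 and ρ = 0.05, is possible but rests on assumed values. For pre-post tests, the inflation depends on how stable facilities are over time and could be absent.

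**What to change.** First, state one unit of analysis for the primary outcomes and make the Sample size, Primary outcomes and Quantitative analysis sections agree on it.

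Second, replace the clustering sentence with a pre-specified method that applies whether or not clustering is detected. Either of these would do:
- facility-level summaries, with inference from between-facility variation; or
- patient-level mixed models, or GEE with variance clustered on facility.

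In both cases, account for district and report the intra-cluster correlations. Suggested wording: *All patient-level proportions and comparisons will allow for clustering by facility, through facility-level summaries or through mixed models or GEE with facility-clustered robust variance; district will be accounted for, and intra-cluster correlations will be reported.* The final text should name which of the two is primary.

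The cost is one replacement sentence and a consistency edit. The routines are standard in R, which the plan already uses. Reported intervals will be somewhat wider: by a factor of about 1.10 to 1.22 at the article's design effects.
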